## Abstract

**Background:**

Lithium is the gold-standard treatment for bipolar disorder, is highly effective in treating major depressive disorder, and has anti-suicidal properties. However, clinicians are increasingly avoiding lithium largely due to fears of renal toxicity. Nephrogenic Diabetes Insipidus (NDI) occurs in 15–20% of lithium users and predicts a 2–3 times increased risk of chronic kidney disease (CKD). We recently found that use of statins is associated with lower NDI risk in a cross-sectional study. In this current paper, we describe the methodology of a randomized controlled trial (RCT) to treat lithium-induced NDI using atorvastatin.

**Methods:**

We will conduct a 12-week, double-blind placebo-controlled RCT of atorvastatin for lithium-induced NDI at McGill University, Montreal, Canada. We will recruit 60 current lithium users, aged 18–85, who have indicators of NDI, which we defined as urine osmolality (UOsm) < 600 mOsm/kg after 10-h fluid restriction. We will randomize patients to atorvastatin (20 mg/day) or placebo for 12 weeks. We will examine whether this improves measures of NDI: UOsm and aquaporin (AQP2) excretion at 12-week follow-up, adjusted for baseline.

**Results:**

Not applicable.

**Conclusion:**

The aim of this clinical trial is to provide preliminary data about the efficacy of atorvastatin in treating NDI. If successful, lithium could theoretically be used more safely in patients with a reduced subsequent risk of CKD, hypernatremia, and acute kidney injury (AKI). If future definitive trials confirm this, this could potentially allow more patients to benefit from lithium, while minimizing renal risk.

**Trial registration:**

ClinicalTrials.gov
NCT02967653. Registered in February 2017.

## Background

Lithium remains the gold standard treatment for bipolar disorder and is associated with a better treatment response in 30–40% of patients compared to other bipolar pharmacotherapies [1, 2]. Lithium is also effective in treatment-resistant depression [1], has been associated with reduced suicidality [3], and is even being investigated in a number of neurological conditions such as dementia and stroke [4, 5]. Lithium is valuable considering the difficulty in achieving and maintaining symptomatic remission in the majority of patients with mood disorders [6]. Furthermore, lithium responders often do not respond well to alternative pharmacotherapies [5]. Rates of disability in people with mood disorders contribute to significant personal, family and societal costs: estimates of these total costs in the U.S. range from $US30–40 billion [7, 8].

Despite the effectiveness of lithium, many clinicians avoid using it, with prescribing rates declining markedly in the past 2 decades, particularly in America where only 8% of bipolar disorder patients receive lithium [9]. This is likely in large part due to the perception of serious potential adverse effects associated with lithium use compared to other treatment options [10].

Of particular clinical concern has been lithium’s potentially irreversible effects on kidney function: in addition to acute kidney injury (AKI), lithium has also been associated with a 2 times increased risk of chronic kidney disease (CKD) [11–13]. CKD, in turn, is associated with increased mortality, physical health co-morbities, decreased quality of life, family/caregiver burden, and major health care costs [14].

The exact mechanism whereby lithium causes CKD is not known. The most prominent pathology seen in patients with CKD attributed to lithium is interstitial nephropathy [15]. This points to a potential link between lithium related NDI and CKD. NDI is characterized by excessive production of dilute urine (> 3 L/24 h) due to tubular resistance to antidiuretic hormone [16]. Half of lithium users have difficulty concentrating urine: e.g. urine osmolality (UOsm) < 600 mOsm/kg following overnight water restriction [15]. Lithium-induced NDI is problematic: in addition to being related to frequent AKI and hypernatremia [17], NDI is also associated with a 2–3 times increased risk of chronic kidney disease (CKD) [12, 17]. Thus, treating lithium-induced NDI could potentially help prevent CKD.

Presently, amiloride is the only medication with evidence from small randomized controlled trials (RCTs) (*n* = 9, *n* = 11) to treat NDI, with a handful of other diuretics and non-steroidal anti-inflammatory agents (NSAIDs) having even lower-quality evidence [15, 18]. However, these drugs have been associated with acute lithium-level elevations of up to 33–50%, which could increase the risk of acute central nervous system and renal toxicity [19, 20]. Therefore, there is a need for novel, well-tolerated treatments for lithium-induced NDI.

In a recent cross-sectional study, we found that statins were associated with a lower risk of NDI amongst lithium users (*n* = 71). In this study, lithium users who were also using statins were at lower risk (0%; 0/17) of developing NDI compared to lithium users who were not on statins (20.4%; 11/54) [21]. Two mice studies also demonstrated the effectiveness of statins in genetic forms of NDI, where statins increased the expression of membrane aquaporin 2 in renal tubules and doubled the urine osmolality [22, 23]. Atorvastatin and other statins are well-tolerated and have minimal adverse effects on cognition and mood [24], but have positive effects on cardiovascular risk prevention [9], making it a palatable medication intervention for patients with mental disorders using lithium. In this present paper, we describe the first RCT to evaluate the effectiveness of atorvastatin for treating NDI in a population of lithium users.

## Methods

### Study design and study sample

This is a double-blind, placebo-controlled RCT examining the effectiveness of atorvastatin versus placebo in the treatment of lithium-induced NDI. The study will take place at three tertiary care mental health sites in Montreal, Canada: Douglas Mental Health University Institute (DMHUI), Jewish General Hospital (JGH) and McGill University Health Centre (MUHC).

The study will involve treatment with atorvastatin (20 mg/day) or placebo over a period of 12 weeks. We are aiming to recruit sixty individuals between the ages of 18 and 85 with any psychiatric diagnosis who are currently taking lithium for at least 2 months and have a urine osmolality < 600 mOsm/kg after 10-h water restriction. We opted for a urinary osmolality of < 600 mOsm/Kg: patients with < 600 mOsm/kg are at risk of future NDI-related complications, such as CKD and they constitute a large percentage of lithium users (50% of patients). Other studies have used similar, if not less conservative definitions for NDI [25], which are nonetheless of clinical importance and utility [15]. Other authors have used similar or more liberal definitions in NDI treatment studies [25].

The full inclusion and exclusion criteria can be found in Table 1.

**Table 1 Tab1:** Inclusion and exclusion criteria

Inclusion Criteria	Exclusion Criteria
Between ages 18–85	Already taking statins (at least 6 weeks prior to screening)
Bipolar Diagnosis in any phase of illness: euthymic, depressed or hypomanic. Any schizoaffective diagnosis.	History of adverse reaction to statins; allergy to statins
Diagnosed with NDI, defined by routine 10 h water restriction urine osmolality < 600 mOsm/Kg	Contraindications to statin use: pregnancy or lactation, use of fibrates and heavy alcohol use
Currently taking lithium medication (at least 2 months)	Inability to give consent or deemed to have moderate-severe cognitive disturbances by treating clinician
Able and willing to give informed consent	Active liver disease
	Baseline LDL level < 1.5

### Recruitment procedures

This study has been approved by the local institutional review board (IRBs) of each participating center. Participants are introduced to the study by their treating physician. Interested participants meet with the study research assistant for more details and written informed consent. Patients are then screened for NDI (< 600 mOsm/Kg after 10 h of water-restriction) by their treating clinicians as part of routine clinic visits or by the research assistant in a subsequent visit. Participant flow through the study is described in Fig. 1a and b.

**Fig. 1 Fig1:**
[figure not shown]
**a** Flow chart – Flow of Study Participants through the RCT. **b** Consort diagram for reporting randomized controlled trials (Eldridge et al., 2016 [40])

### Overview of study procedures

In this double-blind RCT, sixty patients will receive 12 weeks of either treatment (20 mg/day atorvastatin) or placebo. The study will require three visits at baseline, 4-week and 12-week follow-up, for which participants will be compensated. During each visit, blood and urine samples after 10 h of water restriction and 12 h of fasting will be requested. In addition to the primary and secondary outcomes, patients will be monitored for safety using blood tests for liver function (AST and ALT), cholesterol (e.g. low-density lipoprotein (LDL)) and lithium toxicity (lithium levels, estimated glomerular filtration rate (eGFR)). Patients will also complete questionnaires about their medical history and mental health. Mood assessments for depression and mania symptoms will be completed at baseline, 4-week and 12-week follow-up, including the Montgomery-Asberg Depression Rating Scale (MADRS) [26], Young Mania Rating Scale (YMRS) [27], and the Quick Inventory of Depressive Symptoms, Self-report-16 (QIDS-16) [28], Altman Self-Rating Mania Scale (ASMRS) [29].

The primary outcome is change in 10 h water restriction urine osmolality (mOsm/kg) and will be assessed at baseline, 4-week and 12-week follow-up visits (Table 2).

**Table 2 Tab2:** Baseline and follow-up visits schedule of events and assessments

Assessment	Screen	Baseline	4-week	12-week
Blood	√	√	√	√
Urine osmolality	√	√	√	√
Medical History	√	√		√
Mood Assessment		√	√	√
1.MADRS		√	√	√
2.YMRS		√	√	√
3. QIDS		√	√	√
4. Altman self-rating mania scale		√	√	√

### Randomization and concealment

After eligibility is confirmed and patients have given consent, patients will be randomized in a 1:1 ratio to receive either 20 mg per day of atorvastatin (treatment group) or placebo (control group). We are using a stratified randomization, with two strata: 1. Diagnosis (bipolar disorder, other diagnosis (e.g. depression, schizoaffective disorder), and 2. McGill hospital site (Douglas Mental Health Institute, Jewish General Hospital (JGH), and McGill University Health Centre (MUHC)). An independent entity, the Lady Davis Institute Data Management Unit is responsible for setting up data management software (Redcap) and randomization. Allocation of participants to groups is concealed in an envelope that only the pharmacy at the Douglas Institute has access to. The patients, clinicians, researcher and outcome assessors will all be blind to the treatment allocation. An independent statistician will perform the statistical analyses.

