#### Planned analysis

We will use independent two-tailed Student’s t-test (or non-parametric equivalent) to compare the primary outcome (raw score values of urinary osmolality at 12-weeks, adjusted for baseline) and secondary outcomes (self-reported fluid intake and variation in aquaporin 2 protein abundance in urinary exosomes at 12-week follow-up, adjusted for baseline) between the treatment (atorvastatin) and control (placebo) groups. The consensus in the statistics RCT literature is that clinical trial outcomes should not be “change from baseline”, but rather the raw score of an outcome, adjusted for the baseline value [37]. Randomization is expected to balance potential confounders between the treatment and placebo groups since both groups are anticipated to have roughly equal baseline characteristics, which we will assess using t-tests (or non-parametric equivalent) and chi-squared tests, as appropriate. However, in the event that any important baseline characteristic differs between groups, we will use multiple linear regression to control for that particular characteristic.

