#### Sample size justification

On repeated measures ANOVA, 60 study completers will allow us to observe an effect size of 0.34 at two-tailed alpha = 0.05 and Power (1-Beta) =0.8 [38]. In our previous cross-sectional findings in chronic lithium users, the effect size of statins on NDI was 0.33 [21], however that was not an intervention study. We acknowledge that there is relatively little data at the current time to justify the sample size. This RCT will provide the necessary and adequate data to plan a subsequent larger RCT [39].

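### Randomisation is stratified by diagnosis and site, but the stated analyses omit both factors; precision is understated to the extent that they predict 12-week osmolality beyond baseline

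*Protocol article*

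**What the plan says.** Protocol article, Randomization and concealment: "patients will be randomized in a 1:1 ratio", and "We are using a stratified randomization, with two strata: 1. Diagnosis", split into bipolar disorder and other diagnoses. The second factor is "McGill hospital site (Douglas Mental Health Institute, Jewish General Hospital (JGH), and McGill University Health Centre (MUHC". That makes 2 × 3 = 6 cells, averaging 60 / 6 = 10 patients each.

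Protocol article, Planned analysis: "We will use independent two-tailed Student’s t-test (or non-parametric equivalent) to compare the primary outcome", where the outcome is described as "raw score values of urinary osmolality at 12-weeks, adjusted for baseline". The same test is named for the two secondary outcomes, fluid intake and urinary aquaporin 2. The only route by which a further covariate can enter is conditional: "in the event that any important baseline characteristic differs between groups, we will use multiple linear regression to control for that particular characteristic".

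No section of the article places diagnosis or site in an analysis.

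**The concern.** Balancing the arms within strata removes between-stratum variation from the treatment difference. If the strata are prognostic, the estimate is then more precise than under simple randomisation. An analysis without the stratification factors still counts that variation as error. Its standard error is then too large, its interval too wide, and its type I error below the nominal 5%.

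The covariate rule makes this worse. It admits a factor only when the arms are seen to differ on it, and the stratification factors are the ones least likely to differ because the design balances them. So the stated rule tends to leave out the two covariates with the best claim to be in the model.

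At stake is some power in a 60-patient trial, and the precision of the estimate it will hand to the larger trial it is meant to inform. False positives are not at stake, because the error is conservative.

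**Working it through.** **Inputs from the article.** 60 completers, 1:1 (30 per arm); six diagnosis-by-site cells; two-sided alpha 0.05; effect size 0.34.

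**Assumed, because the article gives no figure.** Strata explain a share v = 0, 10 or 20% of 12-week variance; baseline correlation 0.5; permuted blocks of 4 within cells. In the simulations for step 2 and for the first and last two rows of the table, diagnosis was split 70/30 and site 50/25/25. The effect size type is not stated; 0.34 is read as Cohen's f, so d = 2 × 0.34 = 0.68.

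**1. The plan's own power figure.** Sample size justification: "60 study completers will allow us to observe an effect size of 0.34 at two-tailed alpha = 0.05 and Power (1-Beta) =0.8", on repeated measures ANOVA. For the between-group test with m measurements and correlation ρ, the noncentrality is f²·N·m / (1 + (m−1)ρ).
- m = 2, ρ = 0.7: 0.1156 × 60 × 2 / 1.7 = 8.16, power 0.802.
- m = 3, ρ = 0.8: 0.1156 × 60 × 3 / 2.6 = 8.00, power 0.794.
- ρ = 0.5: power 0.849 (m = 2) or 0.887 (m = 3).

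The figure can be reached, but only with a correlation that the article does not state. A plain t-test at d = 0.68 with 30 per arm has power 0.736. That mismatch is a separate matter; d = 0.68 is used below only as a working effect.

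**2. A t-test with no baseline term.** With within-arm SD 1, the reported SE is 2/√60 = 0.258. If the strata are exactly balanced, the true SE is 0.258 × √(1 − v).
- v = 0.10: 0.245, so the reported SE is 1/√0.90 = 1.054 times too large.
- v = 0.20: 0.231, a factor of 1/√0.80 = 1.118.

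Simulation (8,000 null and 5,000 alternative runs) gave reported against true SE of 0.257 vs 0.244 and 0.257 vs 0.234. These ratios, 1.05 and 1.10, are a little smaller because incomplete blocks leave some imbalance. Null rejection was 0.051, 0.039 and 0.032 for v = 0, 10 and 20%. Power without and with the strata was 0.757 vs 0.784 at 10% and 0.753 vs 0.826 at 20%, a loss of about 3 and 7 points.

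**3. What baseline adjustment leaves.** The article says the outcome is adjusted for baseline, so what matters is the stratum share of the variance that remains after adjustment.
- *Strata act only through baseline*: share 0, no inflation.
- *Same stratum effect at baseline and week 12*, within-stratum correlation 0.5: the overall correlation is ρ = v + 0.5(1 − v), which is 0.55 or 0.60. The share is v(1 − ρ)/(1 + ρ), giving 0.10 × 0.45/1.55 = 0.029 and 0.20 × 0.40/1.60 = 0.050. The SE is inflated by 1/√0.971 = 1.015 and 1/√0.950 = 1.026.
- *Strata act on week 12 independently of baseline*: share v/(1 − 0.25) = 0.133 and 0.267. The SE is inflated by 1/√0.867 = 1.074 and 1/√0.733 = 1.168.

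**4. Simulated power of baseline ANCOVA at d = 0.68.**

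| How strata act | v | Power without strata | Power with strata | Change (points) |
|---|---|---|---|---|
| Not prognostic | 0% | 0.837 | 0.835 | −0.3 |
| Through baseline | 10% | 0.837 | 0.834 | −0.3 |
| Through baseline | 20% | 0.852 | 0.844 | −0.8 |
| Same at baseline and week 12 | 10% | 0.874 | 0.879 | +0.5 |
| Same at baseline and week 12 | 20% | 0.897 | 0.907 | +1.0 |
| Independent of baseline | 10% | 0.861 | 0.890 | +2.9 |
| Independent of baseline | 20% | 0.875 | 0.934 | +5.9 |

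Type I error without strata was about 4.6–5.7% in the through-baseline and same-effect cases, so close to nominal. In the independent case it was about 3.7–3.8% at v = 10% and 2.5–2.8% at v = 20%. The middle four rows come from 3,000 runs each, with a Monte Carlo standard error near √(0.85 × 0.15/3000) = 0.0065, so changes below 1 point are practically nil.

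**The case against.** The strongest reply is that the planned outcome is already baseline-adjusted. Baseline osmolality is the same measurement on the same patients at the same sites, so a stable site or diagnosis difference is already largely captured by it. This stands: it reduces the loss to about 1 point or less unless the strata act on week 12 separately from baseline.

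The article also gives no reason to expect strong stratum effects. The factors it links to NDI under Baseline demographic and clinical characteristics do not include diagnosis or site. The three sites are hospitals in one city, and entry below 600 mOsm/kg narrows the spread at baseline. This stands too, and it is why the range must start at zero.

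The error is conservative, the effect estimate is not biased by it, and the trial is described as preliminary. All true; these limit the weight of the point.

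A last defence is that a condensed article leaves the covariate list to an analysis plan that is not shown, and that t-test here is shorthand, since a t-test cannot itself adjust for baseline. This holds only in part. The article does not stay silent: it names the test, names baseline as the adjustment, and gives a rule for further covariates that works against the stratification factors.

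**Conclusion.** The mismatch between design and analysis is real, and its consequence is conditional. To the extent that diagnosis and site predict 12-week osmolality beyond baseline, reported standard errors are too large and the test is conservative. On the assumptions above, the power lost by omitting them runs from nil, through about 1 point, to 3–7 points in the least favourable case, with type I error between about 5% and 3%.

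A reader might infer two stronger things. One is that the standard errors are simply wrong for this design. The documents do not support that, because they say nothing on how prognostic the strata are, and the excess is zero if they are not prognostic or act only through baseline. The other is that stratifying achieves nothing. That does not follow either: the arms remain balanced and the estimate keeps its lower true variance. What may be missed is only the credit for that precision in the test and interval.

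This is a low-cost improvement to the analysis and does not threaten the trial's validity.

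**What to change.** Replace the t-test and the conditional covariate rule, for this purpose, with one pre-specified linear model: 12-week osmolality on treatment, baseline osmolality, diagnosis (two levels) and site (three levels), fitted whatever imbalance is observed. Use the same form for aquaporin 2 and fluid intake, each with its own baseline value. Enter main effects only, because the six cells average 10 patients.

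The cost is one sentence in the plan and three degrees of freedom (one for diagnosis, two for site), which takes the residual from 60 − 3 = 57 to 54. If the strata turn out not to be prognostic, the power given up is under about 1 point (0.837 to 0.835 in the simulation). No new data are needed, since both factors are recorded at randomisation. Naming this model also settles how the baseline adjustment is to be done, which a t-test leaves open.

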### Assessments

#### Outcomes measures

Our primary outcome will be urinary osmolality after 10-h water restriction. This short-period water restriction was selected given that longer periods of water restriction are often poorly tolerated by patients, especially those on lithium treatment [30]. Clinically, the 10-h water restriction assessment of urine osmolality is often used and is highly specific and sensitive for NDI [25, 31, 32]. We will assess the raw urine osmolality value at 12-weeks, adjusted for baseline. An increase in urine osmolality (mOsm/Kg) values adjusted for baseline will be indicative of improvements in the kidney’s ability to concentrate urine [33, 34]. We hypothesize that higher osmolality values will be observed compared to baseline in patients randomized to atorvastatin.

We chose measures of aquaporin 2 excretion and self-reports of daily fluid intake as the secondary outcomes. Aquaporins are channels involved in water reabsorption in the collecting ducts of the kidney [35]. Assessment of aquaporin excretion in urine will be indicative of the expression of the aquaporin channels and water reabsorption capabilities of the kidneys, allowing further confirmation of whether: 1) NDI pathology is present and 2) whether it is being modified by atorvastatin treatment. Furthermore, changes in daily fluid intake have been highly correlated with both urinary osmolality and the gold-stand as a characteristic of NDI [30, 31, 36]. Additionally, we supplement these secondary measures with self-reported frequency of nighttime and daytime polyuria.

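### Two pre-treatment urine osmolality values are scheduled, but the primary outcome is adjusted for one undefined baseline: a modest missed efficiency, not a bias

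*Protocol article*

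**What the plan says.** All references are to the protocol article.

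- **Outcomes measures** gives the primary analysis: "We will assess the raw urine osmolality value at 12-weeks, adjusted for baseline". Planned analysis repeats the phrase and names the test: "We will use independent two-tailed Student’s t-test (or non-parametric equivalent) to compare the primary outcome". Multiple regression is foreseen only if an important baseline characteristic differs between groups.
- **Overview of study procedures** says that the primary outcome "will be assessed at baseline, 4-week and 12-week follow-up visits". Screening is not in that list.
- **Table 2**, titled "Baseline and follow-up visits schedule of events and assessments", ticks urine osmolality in separate Screen and Baseline columns.
- The text above Table 2 counts no screening visit: "The study will require three visits at baseline, 4-week and 12-week follow-up, for which participants will be compensated".
- **Recruitment procedures** allows the screening measurement to be made "by their treating clinicians as part of routine clinic visits or by the research assistant in a subsequent visit". The same value decides eligibility (below 600 mOsm/kg).

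**The concern.** The adjustment is there to remove between-patient variation from a comparison of about 30 patients per arm. A single overnight-restricted sample measures a patient's concentrating ability imperfectly, and a second pre-treatment sample carries further information on it. Table 2 provides that second sample, yet the outcome description points to one baseline and does not define it.

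Two things follow. Some precision that needs no new visit or sample may go unused. In addition, the only covariate named for the primary outcome is not tied to a particular collection, although one of the two candidates has been selected to lie below 600 and the other has not.

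**Working it through.** **The plan's own figure.** The article gives no figure for the value of baseline adjustment. Its only related number is under Sample size justification: "60 study completers will allow us to observe an effect size of 0.34 at two-tailed alpha = 0.05 and Power (1-Beta) =0.8". The number of measures and the correlation behind it are not stated, so it cannot be reproduced uniquely. Read as Cohen's f for a between-groups effect with N = 60, it is reached with two measures at correlation 0.7 (0.339) or three measures at 0.8 (0.342). It does not bear on how the screening value is used.

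**Inputs from the article.** 60 patients, 1:1; entry on screening osmolality below 600; about half of lithium users below 600 (Study design and study sample), so the population is centred at 600.

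**Assumed inputs.** Normal distributions; between-patient SD 100 or 150; within-patient SD 75 to 150 mOsm/kg; independent errors between visits.

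**Step 1. No entry selection.** With equal correlation ρ between visits, the residual variance factor is 1 − ρ² with one pre-treatment value and 1 − 2ρ²/(1 + ρ) with two.

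- ρ = 0.5: 0.750 and 0.667, ratio 0.889.
- ρ = 0.7: 0.510 and 0.424, ratio 0.830.

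These cuts of 11% and 17% are too favourable, because the screening value is cut off at 600.

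**Step 2. With entry on screening < 600.** Simulation of 2,000,000 patients per case. True level T ~ N(600, between SD); screening, baseline and week 12 are each T plus error; only patients with screening < 600 are kept. Patients gained = 60 × (1/ratio − 1).

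| Between SD | Within SD | Reliability | Residual variance, both vs baseline alone | Worth, of 60 |
|---|---|---|---|---|
| 150 | 75 | 0.80 | 0.868 | 9.1 |
| 150 | 100 | 0.69 | 0.905 | 6.3 |
| 150 | 125 | 0.59 | 0.931 | 4.4 |
| 150 | 150 | 0.50 | 0.949 | 3.2 |
| 100 | 75 | 0.64 | 0.919 | 5.3 |
| 100 | 100 | 0.50 | 0.949 | 3.2 |
| 100 | 125 | 0.39 | 0.966 | 2.1 |
| 100 | 150 | 0.31 | 0.978 | 1.3 |

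The cut is therefore about 2–13%. With equal errors, the mean of the two values and two separate covariates give the same result.

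**Step 3. Noisier screening sample.** Same model, with a larger error for screening only.

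| Between SD | Within SD, baseline and week 12 | Within SD, screening | Mean vs baseline alone | Two covariates vs baseline alone |
|---|---|---|---|---|
| 150 | 75 | 150 | 1.09 | 0.963 |
| 150 | 100 | 200 | 1.07 | 0.973 |
| 150 | 125 | 200 | 1.00 | 0.970 |
| 150 | 100 | 150 | 0.99 | 0.953 |
| 150 | 150 | 225 | 0.99 | 0.975 |
| 100 | 100 | 200 | 1.04 | 0.985 |

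Two covariates still gain, by about 1–5%. The mean forces equal weights and can raise residual variance by up to about 9%.

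**Step 4. Cost of the second covariate.** With k covariates, the variance of the adjusted difference is inflated by about (N − 3)/(N − 3 − k). Going from k = 1 to k = 2 at N = 60 gives 56/55 = 1.018, or about 2%. Net ratios from Step 2 then run from 0.868 × 1.018 = 0.884 to 0.978 × 1.018 = 0.996. At the weakest row of Step 3 the net is 0.985 × 1.018 = 1.003.

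**Step 5. Why the two values are not interchangeable.** In the Step 2 cases, 21–40% of those enrolled read 600 or more at baseline, and the mean rises 27–100 mOsm/kg from screening to baseline with no treatment. The screening value used alone leaves 3.5–8.6% more residual variance than the baseline value alone.

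**Step 6. Scale against the test.** Under the same selection, ANCOVA on a single baseline cuts variance by about 16% (ρ = 0.5) to 32% (ρ = 0.7) against an unadjusted t-test. That is several times what the second value adds.

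**The case against.** The strongest reply is that nothing here is an error. Adjusting for the baseline-visit value is standard and unbiased, and how baseline is derived from several pre-treatment values is often left to an analysis plan. The gain depends on assumed SDs. It is smallest where the measurement is noisiest, which weakens any argument built on noise. A distinct, comparable screening value may not exist for every patient, since the text counts three visits and screening may be done in routine care. All of this stands, and it limits the point to efficiency. What remains is that the article itself schedules two values, lists the outcome visits without screening, and leaves the covariate undefined.

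Three stronger readings are tempting and are not supported:

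- **That the screening value is discarded.** No section says so. The article neither excludes it nor uses it.
- **That sites will carry the qualifying value forward as baseline.** The article asks for a restricted urine sample at each visit, and Table 2 ticks Baseline separately. The three-visit count and the routine-clinic route leave room for doubt, but they do not show that this will happen.
- **That the comparison is biased.** Both values precede randomised treatment, so either choice leaves it unbiased.

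**Conclusion.** The point holds as a modest missed efficiency. Using both pre-treatment values would cut residual variance by about 2–13% if the samples are distinct and of similar quality, and by about 1–5% if the screening sample is noisier, before a cost of about 2% for the extra degree of freedom. At low retest reliability, or with a poor screening sample, the net gain is close to nil. These figures assume normality, independent errors, a population centred at 600, and SDs that the article does not supply.

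The gain also depends on a model that carries covariates. A two-sample t-test does not, and naming such a model matters more than the second value. The request to define baseline stands even if the precision gain proves small.

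**What to change.** 1. State that baseline for the primary outcome is the separate 10-h restricted sample collected at the baseline visit, and that the qualifying screening value does not stand in for it.
2. Name ANCOVA of the 12-week value as the primary analysis, with the baseline-visit value and the screening value entered as two separate covariates.
3. Do not use their simple mean, which can lose precision if the routine-clinic sample is noisier.
4. Say in advance how patients without a distinct screening sample are handled; they contribute no gain.

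The cost is wording and one degree of freedom (about 2% at n = 60), which may offset the gain if retest reliability is low. No sample or visit beyond Table 2 is needed.
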